**Fig. 2 Fig2:**
[figure not shown]
Adapted Numerical Rating Scale for Spasticity (NRS-S)

**Fig. 3 Fig3:**
[figure not shown]
Schedule for 7-day average NRS-S recording

Secondary outcome measures include, the Modified Ashworth Scale (MAS), a 6-point scale that ranges from 0 to 4 where lower scores represent normal muscle tone and higher scores greater severity of spasticity [19]. ARAT, a 19-item observational measure used by physical therapists and other health care professionals assesses upper limb motor performance (coordination, dexterity and functioning). It is comprised of four subscales (grasp, grip, pinch and gross movement) and arranged in order of decreasing difficulty, with the most difficult task examined first, followed by the least difficult task [20]. The MCID for the ARAT is an improvement in the raw score of at least 4 points [21]. The Medical Research Council (MRC) strength scale will be recorded in the affected limb elbow flexor and extensors, from a score of 0 (no visible contraction) to a score of 5 (normal). The Leeds Adult Spasticity Impact Scale (LASIS) is used to assess the impact of spasticity on daily life. It is a measure of passive arm function that is administered by semi-structured interview to the patient or carer. It consists of 12 items of low difficulty that evaluate performance of daily functional tasks in the individual’s normal environment [22]. Quality of life assessments include the EQ-5D-5 L, which asks participants to rate their health in five dimensions: mobility, self-care, usual activities, pain/discomfort and anxiety / depression [23], and the Spasticity-Related Quality of Life 6-Dimensions (SQoL-6D), designed to assess quality of life in relation to upper limb spasticity across six domains (pain/discomfort; involuntary movements or spasms; restricted range of movement; caring for the affected limb; using the affected limb; mobility/balance) [24]. Each dimension is assessed using a five-level scale ranging from 0 to 4, with higher scores meaning worse condition. The Total SQoL-6D score is computed as a linear transformation of the mean of the six dimensions scores to have the Total score ranging from 0 to 100, with the direction of scoring inverted, so that a higher score indicates a better quality of life, in line with other instruments.

Healthcare utilisation is being assessed at baseline, EOT and at each follow-up visit at 6, 12, 24 weeks after end of treatment using a structured questionnaire developed for this study and supported by data abstracted from electronic health records (clinic visits, GP and hospital attendances, medications use).

### Safety reporting

While prior studies have not demonstrated any safety concerns associated with TENS of SHAPES in the management of spasticity [15, 16] safety outcomes will also be reported. The following definitions will be applied in the reporting of adverse events:

#### Adverse event (AE)

any untoward medical occurrence in a patient or clinical study subject. All such events, whether expected or not, will be recorded.

#### Serious adverse event (SAE)

any untoward and unexpected medical occurrence or effect that: (1) results in death, (2) is life threatening (event in which the subject was at risk of death); (3) requires hospitalisation, or prolongation of existing inpatients’ hospitalisation; (4) results in persistent or significant disability or incapacity; (5) causes a congenital anomaly or birth defect. All SAEs will be collected and recorded whether they are ‘related’, that is, resulted from the administration of any of the research procedures, or ‘unexpected’, that is, an event that is not an expected occurrence. In the event of any SAE unblinding will occur to establish potential causality.

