At the second study visit, other baseline outcome measures are completed. Participants in the SHAPES or TENS arms receive a specially designed upper limb electrical stimulation system (ShefStim APS) and are trained on how to apply and use the device each day during the intervention period. All devices are configured to the allocated TENS or SHAPES arms of the study using a QR code to maintain blinding. Participants then deliver the intervention at home independently or with the help of a care giver for 6 weeks. After 2–3 weeks all participants are contacted to check that they are managing the NRS-S diary, with those in the device arms also receive a safety / device review with the study team. At the end of the 6-week intervention period they return for end of treatment outcome measures that also include an assessment of healthcare utilisation. These assessments are repeated at 6 weeks, 12 weeks and 24 weeks after the end of intervention period. All participants are invited to undergo experiential interviews, providing qualitative data on intervention use. While participants and clinicians facilitating the treatment checks will not be blinded to the control group, outcome measures will be undertaken by researchers blinded to treatment allocation, while all participants and researchers undertaking outcome measure assessments will be blinded to type of electrical stimulation.

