### Outcome measures

Clinical examinations of outcome measures are highlighted in Table 2, are collected at baseline, end of treatment (6 weeks), and then 6, 12 and 24 weeks after the end of treatment. These are performed by clinicians with appropriate experience in their application. The primary outcome measure is the.

**Table 2 Tab2:** Study Outcome Measures

**Primary outcome measure** (End of treatment – 6 weeks)	Mean NRS for 7 days.
**Secondary outcome measures**	MAS
	MRC
	Leeds Arm Spasticity Impact Scale
	ARAT
	EQoL 5D-5 L
	SQoL − 6

averaged 7-day NRS-S. This is a simple patient reported level of elbow spasticity where 0 = no spasticity and 10 = worst possible spasticity. This is recorded daily either on paper report forms or digitally according to patient preference. Its validity and reliability in stroke is established as is the minimally important clinical difference (MCID) [18]. Through co-design we have adapted the NRS-S to enable easier completion amongst those with cognitive impairment and aphasia (Fig. 2). The MCID for the NRS-S is a change of ≥ 18% (i.e. 2 points) from baseline to follow up assessment. ^17^ The primary endpoint for this study is the proportion of participants experiencing this MCID improvement in each group. Averaged 7-day NRS-S is calculated at baseline, end of intervention (6 weeks), and then at 6 weeks, 12 weeks and 24 weeks after the end of intervention (Fig. 3).

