### Pre-defined criteria for participant withdrawal

In the event that participants develop any of the following, the intervention will be stopped. Participants will continue to be assessed for outcome measures as per intention to treat analysis.

Patient requiring implantation of new electrical / electronic devices.Patient experiencing a new stroke during intervention period.Allergy to the electrodes or gel.Incidental injury or dermatological condition over the extensor aspect of upper arm.Significant medical illness interfering with delivery of intervention.Pregnancy.

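### The SAE definition builds in expectedness, and any SAE triggers unblinding before causality is judged; the two rules need separating and reconciling with the stated blinding

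*Protocol article*

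**What the plan says.** All of this is in the protocol article.

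- **Serious adverse event (SAE), definition.** An SAE is "any untoward and unexpected medical occurrence or effect that" meets one of five listed seriousness criteria, among them death, hospital admission and lasting disability.
- **Same section, recording.** "All SAEs will be collected and recorded whether they are ‘related’, that is, resulted from the administration of any of the research procedures, or ‘unexpected"; the sentence goes on to define that last term.
- **Same section, unblinding.** "In the event of any SAE unblinding will occur to establish potential causality". No condition on relatedness, expectedness or clinical need is attached, and the recipient of the allocation is not named.
- **Adverse event (AE).** "All such events, whether expected or not, will be recorded".
- **Study procedures.** Outcome measures are taken by researchers blinded to allocation, and "all participants and researchers undertaking outcome measure assessments will be blinded to type of electrical stimulation". No exception for SAEs is mentioned.
- **Outcome measures.** On the primary measure, the NRS-S: "This is a simple patient reported level of elbow spasticity where 0 = no spasticity and 10 = worst possible spasticity".
- **Pre-defined criteria for participant withdrawal.** After the intervention is stopped, "Participants will continue to be assessed for outcome measures as per intention to treat analysis".
- **Statistical analysis and sample size.** SHAPES versus TENS is tested at end of treatment (EOT) and again 6 weeks after EOT.

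**The concern.** There are two separate faults, both in rules that the article states rather than in detail it leaves out.

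The first is classification. Seriousness describes the outcome of an event. Expectedness is a judgement about whether the event was foreseeable. Once the second is a condition of the first, SAE counts by arm depend on a judgement that can vary between assessors. A serious event that someone calls expected falls out of the SAE tabulation, even if it is fatal.

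The second is the order of unblinding and causality assessment. Establishing causality is the stated reason for breaking the code, so relatedness is judged by someone who knows the arm. That can bias the comparison of related events between arms. The rule also reaches events with no plausible link to stimulation, such as an unrelated admission in a population recruited 2 to 26 weeks after stroke.

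Efficacy may also be affected. The primary outcome is the participant's own rating, and participants can be blind only between the two device arms, since usual care has no device. The Discussion presents that blinding as a strength. A participant who learned the pattern would stay in the intention-to-treat comparison with later ratings open to influence. An assessor who learned it would be affected in a similar way on the clinician-assessed secondary measures.

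**Working it through.** **1. The SAE section against itself.** The definition requires an event to be untoward, unexpected and serious. Every SAE is then unexpected by construction. The recording sentence says SAEs are captured whether they are related or unexpected, which has meaning only if some SAEs are neither. Both cannot hold. Taking an expected event that leads to hospital admission:

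| Reading | Recorded as AE? | Classified as SAE? | Triggers unblinding? |
|---|---|---|---|
| Literal definition | Yes (AE section) | No | No |
| Expectedness as an attribute | Yes | Yes | Yes |

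The choice of reading changes both the SAE count and the number of code breaks. The two harms therefore do not add up in full: the literal reading maximises under-classification and reduces unblinding, and the looser reading does the reverse.

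**2. The SAE section against the AE section.** These are compatible. The AE section records all untoward events, expected or not. A narrower SAE class sits inside that set, so an expected serious event loses its SAE label but stays in the data.

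**3. The unblinding rule against Study procedures.** One place says unblinding occurs for any SAE; the other says participants and outcome assessors are blinded to stimulation type. They conflict if the disclosure reaches a participant or an assessor. They are compatible if it reaches only a safety reviewer. The article does not say which.

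**4. How many could be affected.** No SAE rate is stated, so there is no figure of the plan to reproduce. The denominator follows from the design: 297 / 3 = 99 per arm, and 2 × 99 = 198 in the device arms. (The article's own 198 is a different quantity, 3 × 66 for all three arms.)

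Assume that a proportion p of device participants have at least one SAE over 6 + 24 = 30 weeks. At constant hazard, the expected number with an SAE by week t is 198 × [1 − (1 − p)^(t/30)].

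| Assumed p over 30 weeks | By week 6 (EOT) | By week 12 (6 weeks after EOT) | By week 30 |
|---|---|---|---|
| 10% | 198 × (1 − 0.90^0.2) = 4.1 | 198 × (1 − 0.90^0.4) = 8.2 | 19.8 |
| 30% | 198 × (1 − 0.70^0.2) = 13.6 | 198 × (1 − 0.70^0.4) = 26.3 | 59.4 |

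Only events before the week-6 ratings can touch the primary endpoint. Events up to about week 12 can touch the second SHAPES versus TENS test. These counts are upper limits for unblinded ratings under each assumed p, for two reasons: they suppose that the participant or assessor is told every time, and participants who die or are too ill to record give no later ratings.

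**The case against.** The strongest case on the other side is that unblinding for the purpose of causality fits disclosure to a safety reviewer alone, with the blinding in Study procedures intact. Who receives the code and how each break is logged are matters that a condensed article normally leaves to the full protocol, so silence on them is not a fault. The threshold for unblinding is also a trade-off between safety and bias, and the arms do differ in frequency, active electrodes and timing, so a safety reviewer may sometimes want to know the pattern.

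Much of this stands, and it rules out several stronger readings that a reader might infer:

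- *That the SHAPES versus TENS blind is lost in every participant with an SAE.* The article does not say that participants or assessors are told.
- *That some 20 to 59 of 198 device participants would be compromised.* This applies an assumed 10–30% rate over 30 weeks. The rate has no source in the article, no SAE reporting window is stated, and most of that period falls after the primary endpoint.
- *That expected serious events go unrecorded, or that the AE and SAE sections contradict each other.* They are still captured as AEs, and the contradiction lies within the SAE section.
- *That recurrent stroke in particular would be missed.* The article lists no expected events.
- *That SHAPES versus TENS is the only blinded contrast.* This is true for participants. Assessors are blinded to allocation in all three arms.

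The objection does not rescue the two stated rules. Even if only a safety reviewer sees the code, relatedness is judged with the arm known, and the code is broken for events that need no such knowledge. Nor can a fuller document make the definition and the recording sentence agree as they are written.

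**Conclusion.** The point holds in two parts. First, the SAE definition is inconsistent with the sentence that follows it and, taken literally, removes expected serious events from SAE classification and reporting. Second, automatic unblinding for any SAE puts knowledge of the arm ahead of the causality judgement and breaks the code for unrelated events.

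The threat to efficacy blinding is conditional on the participant or assessor learning the allocation. If they do, it bears mainly on SHAPES versus TENS at EOT and 6 weeks after. Its size cannot be derived from the article. On the assumed 10–30% over 30 weeks with constant hazard, about 4 to 14 of 198 device participants would have an SAE by week 6 and about 8 to 26 by week 12, so the effect on the primary endpoint is probably small. No sample size or power figure changes. The correction is worth making because the safety reporting rule is wrong as written and inexpensive to put right.

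**What to change.** 1. In the SAE definition, delete the requirement that the event be unexpected. Record expectedness and relatedness as separate attributes of each SAE.
2. Have causality assessed first without knowledge of the arm.
3. Replace automatic unblinding for any SAE with unblinding only where the event is suspected to be both related and unexpected, or where the allocation is needed for the participant's care.
4. State that disclosure is made outside outcome assessment, so that the SAE section and Study procedures agree. If the full protocol already says this, one clarifying sentence is enough for this item.

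The cost is revised safety wording and a short working instruction. Visits, treatment and sample size are unaffected. Because all adverse events are recorded, events already collected can be checked against the seriousness criteria and reclassified where the record allows. The small downside is that the first causality assessment is made without knowing the stimulation pattern.

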### Pre-defined criteria for participant withdrawal

In the event that participants develop any of the following, the intervention will be stopped. Participants will continue to be assessed for outcome measures as per intention to treat analysis.

Patient requiring implantation of new electrical / electronic devices.Patient experiencing a new stroke during intervention period.Allergy to the electrodes or gel.Incidental injury or dermatological condition over the extensor aspect of upper arm.Significant medical illness interfering with delivery of intervention.Pregnancy.

### Statistical analysis and sample size

Study analysis will be conducted on an intention to treat basis. Baseline characteristics will be presented by treatment group. Summary statistics for each of the endpoints will be reported at each available time point (baseline, EOT, and 6, 12 and 24 weeks after end of treatment). Results will be reported with confidence interval where relevant, for example, in reporting the average difference between treatments in the secondary endpoints. We previously carried out a community-based study using the NRS-S as an outcome measure [16]. Analysis of data from the study was used for the sample size calculation. A change in average NRS-S of 18% from baseline to follow-up time point (MCID) is considered a success. The proportion of successes will be compared between groups (pairwise).

A parallel gatekeeper design has been developed such that the first two significance tests share the total *p*-value equally (each tested at 0.025 level). This will be split equally between the first primary objective (SHAPES vs. usual care, and TENS vs. usual care at EOT (6 weeks) using 2.5% significance each). If one or both of these tests are significant then the *p*-value will be reutilised for testing the second primary objective (SHAPES vs. TENS at EOT and 6 weeks after EOT). This will utilise Chi-squared test (or an exact test if required). Between group efficacy at follow up timepoints (3 and 6 month) will also utilise a continuity corrected Chi-squared test.

We calculated the sample size using data from our previous study [15]. The sample size calculation for a two group t-test for equal means showed that to conduct a three arm randomized control trial of SHAPES, TENS and ‘usual care’ control, we would need 66 subjects per group (total 198 participants) to have 90% power to demonstrate a MCID reduction of 18% in NRS at the 1% significance level to allow for multiple testing. In our feasibility study 67% of participants showed good adherence with the intervention and 73% with recording of NRS. We will recruit a total of 297 patients with PSES to the study who are being randomised to one of the 3 arms. We aim to achieve a minimum of 66 participants to adhere to and complete the protocol in each group with good adherence to the intervention schedule and a minimum of 4 of 7 daily NRS-S recording. This will be known as the Per Protocol Set (PPS). Sensitivity analyses will be conducted to investigate the impact of missing or incomplete data, non-compliance, and spasticity severity. The sample size calculation was done in R using simulations.

Analysis of other secondary objectives (ARAT, MAS, MRC, LASIS, EQ-5D, SQoL-6D) will use repeated measures analysis with treatment group and timepoint as factors, baseline as a covariate and subject as a random effect to investigate the within-participant change in each outcome over time and to see if there is a treatment effect. As some of these outcomes are ordinal, it may not be possible to satisfy the conditions of a repeated measures ANOVA thus Friedman test may be used instead with pairwise Wilcoxon Signed Rank tests for any post-hoc analysis requirements. Since these analyses are exploratory, no adjustment for multiplicity will be made – nor will significant conclusions be drawn.

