### Study procedures

At the screening visit, participant written informed consent is obtained by study researchers, eligibility confirmed by a medical doctor of the study team, demographic data recorded, and a baseline assessment of healthcare utilisation recorded. The participant is trained on recording daily NRS-S for 7 days (baseline assessment), recorded either using a dedicated smartphone ‘App’ or as a paper diary to suit their preference. The average of which (minimum 4 of 7 days scores) forms the baseline 7-day NRS-S score, completed prior to attending Visit 2. The participant is then be randomised (1:1:1) to either:

SHAPESTENSUsual care

**Table 1 Tab1:** Study inclusion and exclusion criteria

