#### SHAPES

Each horizontal row of 8 electrodes on the array is sequentially activated for 0.3s at a pulse repetition frequency of 50 Hz and with a pulse width of 250µs. After all 8 rows of electrodes have operated the stimulation pauses for 2.5s before the sequence is repeated.

The participants in the usual care arm do not receive any device. The systems are programmed following randomisation allocation, using a QR code that is scanned onto a stimulator remote control (repurposed Alcatel 1c smartphone) and delivered via Bluetooth LE to the stimulator box. The participant’s mid-bicep circumference is be measured and the oversized sleeve cut to size to ensure that a personalised sleeve fit is achieved. When applied, the biocompatible hydrogel layer should contact the skin overlying the extensor aspect of the affected upper limb, over the triceps area. During the setup of the ShefStim APS (for those in the SHAPES or TENS arms of the study) the stimulation intensity (current) is gradually increased until the underlying muscle begins to twitch (motor threshold, MT). If the participant experiences any discomfort from the stimulation, the intensity is limited to the highest that is comfortable for them. The stimulation level is then set to 90% of the MT or, if the MT was not reached, 90% of the maximum comfortable level. This intensity is recorded at baseline and becomes the default level for home use. Participants are trained on how to apply the sleeve and, if necessary, adjust the stimulation intensities (within clinically set levels) for comfort.

During the intervention participants can receive all usual cares for spasticity management provided by the NHS (e.g. botulinum toxin, oral agents, stretching exercises etc.). This will be recorded and compared between the 3 groups and adjusted for in the statistical analysis.

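### The primary responder test is valid but ignores the baseline NRS-S already collected before randomisation, and the continuity correction at later follow-up makes those tests needlessly strict

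*Protocol article*

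**What the plan says.** All references are to the protocol article.

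- **Endpoint** (Outcome measures): "The primary endpoint for this study is the proportion of participants experiencing this MCID improvement in each group". Statistical analysis and sample size adds: "A change in average NRS-S of 18% from baseline to follow-up time point (MCID) is considered a success". Outcome measures also glosses the 18% as 2 points.
- **Primary test** (Statistical analysis and sample size): "The proportion of successes will be compared between groups (pairwise"), and then "This will utilise Chi-squared test (or an exact test if required"). No covariate is named.
- **Later follow-up** (same section): the 3 and 6 month comparisons "will also utilise a continuity corrected Chi-squared test".
- **Secondary outcomes** (same section): a repeated measures analysis with "baseline as a covariate and subject as a random effect".
- **Timing of baseline** (Study procedures): the mean of the daily scores "forms the baseline 7-day NRS-S score, completed prior to attending Visit 2. The participant is then be randomised (1:1:1) to either" of the three arms.
- **Concomitant spasticity care** (Interventions and control, end of the SHAPES subsection): "This will be recorded and compared between the 3 groups and adjusted for in the statistical analysis".

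**The concern.** Success is measured against the participant's own starting score, but that does not remove the influence of the starting score. High baselines tend to fall and low ones to rise through regression to the mean. Under the 2-point reading, anyone with a baseline below 2 cannot succeed at all, and the eligibility criteria set no minimum NRS-S. Baseline is therefore likely to be prognostic for success. A test that ignores a prognostic pre-randomisation covariate usually has less power than one that uses it.

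Two inconsistencies sit beside this. The plan gives the exploratory outcomes a baseline-adjusted model and the confirmatory outcome none. It also names a continuity-corrected test for the later comparisons only, so persistence of effect is held to a stricter standard than the effect at end of treatment (EOT).

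At stake are some power for the primary question, power for the persistence objective, and a clear statement of which adjusted analysis will be run.

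**Working it through.** **Inputs from the document.** 297 participants are randomised 1:1:1, so 297 / 3 = 99 per arm. This agrees with the stated 66 per group and 67% adherence: 66 / 0.67 = 98.5, rounded up to 99, and 3 × 99 = 297. Each comparison with usual care is tested at 0.025, taken here as two-sided because the article does not say.

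**Inputs assumed.** The article gives no NRS-S mean, SD, correlation or expected success rates. I take baseline mean 5, SD 2, a true difference of 1 point, and a baseline to follow-up correlation of 0.3, 0.5 or 0.7. Both readings of success are run.

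**Tests compared.** With success proportions p0 and p1, pooled proportion p and n per arm:

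- plain chi-squared: (p1 − p0)² / [2p(1 − p)/n]
- continuity-corrected: (|p1 − p0| − 1/n)² / [2p(1 − p)/n]
- adjusted: logistic regression of success on arm and continuous baseline, with a likelihood-ratio test for arm

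**Power, 3,000 simulated trials per row** (Monte Carlo error at most √(0.5 × 0.5 / 3000) = 0.9 points):

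| Success rule | Correlation | Plain | Corrected | Adjusted | Adjusted minus plain |
|---|---|---|---|---|---|
| 18% fall | 0.3 | 62% | 57% | 69% | +7 |
| 18% fall | 0.5 | 78% | 74% | 82% | +4 |
| 18% fall | 0.7 | 94% | 91% | 95% | +1 |
| 2 points | 0.3 | 47% | 41% | 58% | +11 |
| 2 points | 0.5 | 61% | 54% | 68% | +7 |
| 2 points | 0.7 | 76% | 70% | 80% | +4 |

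An independent repeat gave gains of about 8, 3 and 0 points (18% rule) and 12, 8 and 5 points (2-point rule). Under no effect, the adjusted test rejected in 2.0% to 3.1% of 1,500 trials at a nominal 2.5%, so type I error is kept. A test of the marginal risk difference from the same model performed the same as the likelihood-ratio test.

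**Wider range, 18% rule only.** With 66 or 99 per arm, baseline mean 5.5, SD 2.0 to 2.98, differences of 1 to 2 points and correlations of 0.3 to 0.85, the gain ran from −0.4 to +7.5 points and was about zero at 0.7 and above. The reason shows in the control arm: at SD 2, the correlation between baseline and success is about 0.36, 0.25, 0.11 and −0.06 when the score correlation is 0.3, 0.5, 0.7 and 0.85. Once the scores track closely, the percentage change has already absorbed most of what baseline can tell.

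**Continuity correction.** Take n = 99, p = 0.40 and a nominal two-sided 5% level (the article states no level for these comparisons). The standard error is √(2 × 0.40 × 0.60 / 99) = 0.0696. The plain test needs a difference of 1.96 × 0.0696 = 0.136. The corrected test needs 1/99 = 0.010 more, about 0.147. Summing exact binomial probabilities, the true size of the corrected test at 99 per arm is 0.033, 0.035 and 0.039 for common success rates of 0.25, 0.40 and 0.50. At 66 per arm it is 0.029 to 0.032. The plain test stays between 0.045 and 0.055. In the table the correction costs 3 to 7 power points.

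**Adjustment for concomitant care.** The interventions section promises that this care will be adjusted for. The analysis section names a two-by-two test for the primary endpoint, which has no place for a covariate. The two statements cannot both describe the primary analysis.

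**The case against.** The strongest reply is that nothing here is wrong. An unadjusted chi-squared test between randomised arms is valid, and its error rate already allows for chance imbalance in severity. A reader might infer that imbalance biases the result, the more so as no stratification is stated. The document does not support that: chance imbalance is sampling variation, and an article may leave stratification factors to the full protocol. This objection stands, and it limits the point to efficiency.

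A reader might also infer that substantial power is thrown away. That does not follow either. Every simulation input is an assumption, the endpoint already uses baseline through the change, and the larger gains need the 2-point reading, which appears only as a gloss; elsewhere the article speaks of 18%.

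A third tempting inference is that the change of test makes persistence results non-comparable with EOT. It does not, because the success proportions and their differences are the same whichever test is used. The correction is stated only for secondary time points, so its cost is not a loss on the primary question. The wording could even be shorthand for one test throughout, in which case the correction would reach the primary test as well and needs clarifying.

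Finally, the article plans sensitivity analyses for spasticity severity, and an unseen analysis plan may name covariates. That softens the point but does not remove it: the article itself fixes the primary test.

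**Conclusion.** The point holds as an efficiency and consistency improvement. It is not an error of validity or a source of bias. Adjusting the primary comparison for baseline NRS-S adds about 0 to 8 power points under the 18% rule and about 4 to 12 under the 2-point gloss, for 99 per arm, baseline mean 5, SD 2, a 1-point effect, two-sided 2.5% and correlations of 0.3 to 0.7. If the true correlation is 0.7 or more under the 18% rule, the gain is near zero, but so is the cost in power. The continuity correction is needlessly conservative at this sample size (3.3% to 3.9% for a nominal 5%) and affects the secondary persistence tests. The conflict between the promised adjustment for concomitant care and the named test is a matter of text and depends on no assumption.

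**What to change.** Before unblinding, amend the protocol and analysis plan as follows.

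1. Make the primary test a logistic regression of success on arm and continuous baseline 7-day NRS-S, reported as a marginal (standardised) risk difference with confidence interval. Leave the significance levels and testing order unchanged.
2. Use the same model at EOT and at 6, 12 and 24 weeks after EOT.
3. Drop the continuity correction, and keep the uncorrected chi-squared test as a sensitivity analysis.
4. Reconcile the statement on concomitant spasticity care with the analysis section, by naming the analysis in which the adjustment is made or by withdrawing the promise. Care received during the intervention is recorded after randomisation and may depend on arm, so a supporting analysis is the natural place for it. Baseline NRS-S does not have that difficulty.

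No new data are needed, since a baseline score is already required of every participant. The cost is an amendment to a primary analysis in a trial whose recruitment was planned from June 2023 to December 2024, plus a little more analysis work. The amendment should be dated and should record that it was made without sight of results by arm.
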